# Effect of superficial and deep parasternal blocks on recovery after cardiac surgery: study protocol for a randomized controlled trial

**DOI:** 10.1186/s13063-023-07446-2

**Published:** 2023-07-06

**Keywords:** Cardiac surgery, Anesthesia, Regional anesthesia, Quality of recovery, Patient related outcomes, Superficial parasternal intercostal plane block, Deep parasternal intercostal plane block

## Abstract

**Background:**

Pain is frequent after cardiac surgery and source of multiple complications that can impair postoperative recovery. Regional anesthesia seems to be an interesting technique to reduce the pain in this context, but its effectiveness in improving recovery has been poorly studied so far. The objective of this study is to compare the effectiveness of two of the most studied chest wall blocks in cardiac surgery, i.e., the superficial and the deep parasternal intercostal plane blocks (SPIP and DPIP respectively), in addition to standard care, versus the standard care without regional anesthesia, on the quality of postoperative recovery (QoR) after cardiac surgery with sternotomy.

**Methods:**

This is a single-center, single-blind, controlled, randomized trial with a 1:1:1 ratio. Patients (*n* = 254) undergoing cardiac surgery with sternotomy will be randomized into three groups: a control group with standard care and no regional anesthesia, a SPIP group with standard care and a SPIP, and a DPIP with standard care and a DPIP. All groups will receive the usual analgesic protocol. The primary endpoint is the value of the QoR evaluated by the QoR-15 at 24 h after the surgery.

**Discussion:**

This study will be the first powered trial to compare the SPIP and the DPIP on global postoperative recovery after cardiac surgery with sternotomy.

**Trial registration:**

ClinicalTrials.gov NCT05345639. Registered on April 26, 2022.

**Supplementary Information:**

The online version contains supplementary material available at 10.1186/s13063-023-07446-2.

## Background

Every year, more than one million people around the world undergo heart surgery by sternotomy [1]. Postoperative pain is frequent after sternotomy, especially in the first 48 h following surgery [1]. The occurrence of this pain is multifactorial [2] and associated with other postoperative complications (e.g., nausea and vomiting, confusion, arrhythmia, myocardial infarction), compromising the early quality of recovery (QoR) and increasing postoperative mortality. In the first postoperative days, this pain is commonly treated with intravenous analgesics including opioids [3], for which side effects may also impair the overall quality of recovery [4].

A multimodal analgesic strategy aiming at sparing opioids, including the use of a peripheral nerve block (PNB) [5], has already shown its usefulness in cardiac surgery [6]. The most recent guidelines of the French Society of Anesthesia and Intensive Care Medicine (SFAR) concerning enhanced recovery after surgery in cardiac surgery highlighted the use of PNB [7]. Among the several techniques of PNB assessed in cardiac surgery, the most promising ones are those based on fascial plane blocks, especially the superficial parasternal intercostal plane block (SPIP) and the deep parasternal intercostal plane block (DPIP), for which frequent names were the pectoral parasternal block [8, 9] and the transversus thoracic muscular plane block [10–12] respectively before the recent standardized nomenclature proposed by the ASRA-ESRA Delphi consensus [13].

In comparison with the SPIP, the DPIP allows the injection of local anesthetic closest to the anterior branches of the intercostal nerves and may be theoretically more efficient. However, there is currently one randomized trial only comparing SPIP and DPIP, which found no difference between the two blocks [14]. Furthermore, while all of these evaluations have focused mainly on pain intensity and opioid consumption, there are no study assessing the impact of the use of a SPIP or a DPIP on the early postoperative quality of recovery.

We aim to compare the effectiveness of the use of a SPIP or a DPIP in addition to standard care, in comparison with standard care without regional anesthesia on the early postoperative QoR after cardiac surgery with sternotomy.

## Methods

This is a superiority, single-center, single-blinded, controlled, randomized trial in which patients undergoing cardiac surgery by sternotomy will be included. The patients will be randomized into three groups, either in the SPIP group (receiving a SPIP in addition to standard care), the DPIP group (receiving a DPIP in addition to standard care), or the standard group (receiving standard care but no regional anesthesia). The study will be conducted at the Angers University Hospital (Angers, in France). This trial is designed according to the elements of the standard protocol (SPIRIT guidelines). Figures 1 and 2 provide an overview of the study plan.

**Fig. 1 Fig1:**
[figure not shown]
Standard Protocol Items: Recommendations for Interventional Trials (adapted from SPIRIT figure). Abbreviations: NRS, numerical rating scale, FQoR-15, French version of the QoR-15; V1/2/../9, visit 1/2/../9; H + 3/…/ + 120, 3/…/120 h at surgery; D30, 30 days at surgery

**Fig. 2 Fig2:**
[figure not shown]
Flow chart

The French Institutional Review Board North-West IV (Lille, France, reference number: 2022-A00238-35) and the National Agency for Drug and Health Product Safety have approved the study protocol (2022-A00238-35) in its version 4. Patients will provide written consent for participation. The study will be conducted in accordance with the Declaration of Helsinki.

### Participants

Eligible participants are adults (≥ 18 years old) who are going to have cardiac surgery with sternotomy. Eligible patients must be French-speaking and must have the sufficient cognitive ability to complete a questionnaire. Exclusion criteria are known hypersensitivity to local anesthetics, redo heart surgery, emergency surgeries, septic context (endocarditis, intravascular device infection), weight less than 30 kg, psychiatric disorder or severe cognitive impairment hampering assessment by questionnaires, pregnant/breastfeeding/parturient women, persons deprived of their liberty by judicial decision or subjected to psychiatric treatment under duress, and inclusion in another interventional study modifying postoperative pain management. Inclusion will be confirmed at the end of the surgery (i.e., time of the skin suture), in the absence of hemodynamic instability (defined here as a norepinephrine infusion equal or greater than 1 μg/kg/min) and in the absence of bleeding requiring immediate surgical revision.

### Information of patients

During the anesthesia consultation (about 2 weeks before surgery), investigators will invite the patients to participate after verification of the inclusion/exclusion criteria. Patients will receive complete information in faithful terms and understandable language concerning the objectives, the required follow-up, the risks, the safety measures, and the rights to refuse to participate or stop the study at any time. A written informed consent will be signed by both the investigator and the patient. If a longer reflection time is desired, the proposal to participate in the study will be again done to the patient during the pre-surgical visit (the day before or the day of surgery).

### Randomization and blinding

The anesthesiologist in charge will perform the randomization at the end of the surgy in the operating room. The included patients will be randomized using a 1:1:1 ratio in one of the three groups (SPIP group, DPIP group, or standard group). The randomization will be stratified on the achievement or not of an internal thoracic artery graft, as patients having cardiac surgery with internal thoracic arteries are more susceptible to present postoperative acute or chronic pain [15]. The investigators will use the Ennov Clinical® software and will not know the stratification process to avoid guessing the next allocation.

The anesthesia team in charge of the patient in the operating room will be unblinded to the allocation group. Conversely, patients will not know in which group they have been allocated since the block (SPIP or DPIP) will be performed at the end of the surgery, under general anesthesia. To maintain the blinding for the medical and paramedical team in charge of the patient in the intensive care unit, a skin dressing in accordance with the puncture zone will be used for all patients, even for those in the standard group.

### Intervention

This study aims to compare the added effect of parasternal intercostal plane block (SPIP or DPIP) to postoperative standard care. SPIP and DPIP will be performed under general anesthesia in the operating room at the end of the surgery, once the skin closure has been finalized. For skin disinfection, we will use the same antiseptic as for the surgical procedure. The anesthetist performing the procedure will wear sterile gloves, with a mask and a surgical cap. According to the French Society of Anesthesia and Intensive care Medicine (SFAR) recommendations [16, 17], an ultrasound protection and sterile ultrasound gel will be used to perform the block under ultrasound guidance (sagittal section, with a 7.5 MHz ultrasound probe). A 50-mm regional needle with a diameter of 22G will be used. For both types of blocks, the anesthetist should position the probe next to the sternum and laterally move the probe to identify the internal thoracic artery using the color Doppler. When this artery is observed, both techniques consist in puncturing in the craniocaudal plane at 2 cm from the sternum laterally, next to the space between the 4th and 5th ribs.

For the DPIP, the injection is performed between the internal intercostal muscle and the transverse thoracic muscle (20 mL of 0.2% ropivacaine). The lowering of the pleura during the injection is a quality sign [18]. The same injection has to be performed on the other side of the sternum. For the SPIP, the same process is realized but the injection of ropivacaine should be performed between the major pectoral muscle and the external intercostal muscle (20 mL of 0.2% ropivacaine on each side).

Each patient in each of the three groups will be operated on under general anesthesia and will receive standard management with a radial artery catheter for continuous blood pressure monitoring, two peripheral venous catheters, a central venous catheter (right or left internal jugular catheter), and a temperature-sensing indwelling urinary catheter. The anesthetic induction will be performed using total intravenous anesthesia (TIVA) as follows: propofol with plasma target at 2–4 μg/mL, sufentanil with brain target at 0.4–1 ng/mL, an intravenous (IV) bolus of atracurium 0.3 to 0.6 mg/kg, and dexamethasone 8 mg IV. For the anesthesia maintenance, the sufentanil brain target will be set at 0.2–0.8 ng/ml, depending of the different times of the surgery, and inhaled sevoflurane will be used with a minimum alveolar concentration (MAC) objective of 1 during the non-cardiopulmonary bypass period although propofol TIVA only will be used during the cardiopulmonary bypass period.

At the end of the surgery, the patient will be transferred to the intensive care unit (ICU) under intravenous propofol sedation, as usual. The pain management protocol in ICU is detailed in the supplementary material (Table S.1).

### Outcomes

#### Primary outcome

The primary endpoint is the early postoperative QoR, assessed via the French version of the QoR-15 questionnaire score (FQoR-15) [19] and measured at 24 h after the surgery (H24). The Quality of Recovery-15 (QoR-15) is one of the most reliable and reproducible tools for assessing the QoR after surgery [20–22]. The use of this tool as an endpoint has been recommended by a recent international consensus [23] and has already been measured in previous randomized trials [24].

The FQoR-15 is obtained via a self-administered questionnaire, consisting of 15 items scored on an 11-point scale with an overall score (sum of each item) ranging from 0 to 150 (0 for very bad recovery, 150 for excellent QoR). The questionnaire will be given by the nurses to the patient in ICU on a paper sheet that will be filled out by the patient.

#### Secondary outcomes

In order to evaluate the impact of a SPIP or DPIP on the QoR, we will also reassess the QoR-15 score at 48 h (H48) and 72 h (H72) after the surgery. We will compare analgesic efficacy at rest and during exercise (cough, physiotherapy, mobilization) between the different groups via a pain intensity evaluation using a numeric rating scale (NRS, 11 items, 0 for no pain and 10 for the maximum pain) up to H72 after the surgery and during the removal of the drains at 24 h after surgery (H24). We will specify the proportion of painful patients (defined by an NRS value > 3) at H24 and H48. We will also collect the main area of pain during the first 24 h after surgery between the back, the head, the thorax, the abdomen, and the saphenous scar. We will also compare the postoperative consumption of analgesics (both morphine equivalents and non-opioid drugs) up to 5 days after the surgery.

The tolerance of the technique will be compared by assessing the proportion of patients with at least one local complication of regional anesthesia: systemic intoxication to local anesthetics within 3 h after injection, hematoma or infection at the puncture site during the 30 days after the surgery (D30). We will also compare in each group the proportion of patients with at least one major hospital postoperative complication [25] (the complete list is presented in Table S.2 in the supplementary materials).

We will assess in each group the proportion of patients with a return to preoperative weight, as the proportion of patients with bowel movements assessed on days 3 and 5 after surgery. We will compare the delay of extubation (measured between the admission in ICU and the first attempt of extubation), the length of stay in ICU, and the length of hospital stay censored at D30 if the patient is still hospitalized. The readmission rate in ICU will be specified at D30.

The anesthetist’s satisfaction with the ease of performing the technique (i.e., DPIP or SPIP) will be evaluated on a 5-item Likert scale (not at all satisfied, not very satisfied, neutral, fairly satisfied, very satisfied) and compared between the two intervention groups with blocks.

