### Safety

The major potential adverse effects linked to SPIP and DPIP are pneumothorax, mediastinitis, hematoma, puncture site infection, and intoxication with ropivacaine [27–29]. Continuous monitoring of vital parameters within 3 h following the PNB procedure will be carried out to detect local anesthetic toxicity. A chest X-ray is systematically realized at ICU admission, and this investigation will allow to detect the presence of a pneumothorax. The body temperature will be noted every 3 h by a nurse, and the monitoring of the occurrence of complications at the puncture site will be done at each visit up to D30. The occurrence of a serious adverse event will be collected at any time during the patient’s follow-up (up to 30 days), whose imputability with one of the allocation groups will be discussed.

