For all analyses using regression models, the included covariates will be the allocation group, as well as the stratification group (surgery with or without thoracic internal arterial graft). For analyses requiring a mixed model, the covariates introduced will be a fixed effect for the treatment arm, a fixed effect for the stratification factor, a fixed effect for the time frame of the visit, and a random effect for the patients, and under an unstructured variance/covariance matrix. If the mixed models do not converge, we will use a compound symmetry correlation structure. To address the main objective, we will use a linear regression model. Similarly, the QoR-15 score at H48 will be analyzed using a linear regression model. The evolution of effort pain up to H48 will be analyzed using a linear mixed model. The evolution of morphine equivalent consumption will be analyzed using a mixed model, following a Poisson distribution. The rate of occurrence of at least one postoperative complication will be compared by logistic regression. Censored 30-day hospital stay will be assessed by survival analysis using a semi-parametric Cox model.

The other endpoints will not have a method of imputation for missing data. Thus, only those individuals for whom endpoints are available will be included in the analyses. These data will be analyzed for exploratory purposes. The evolution of pain at rest will be analyzed with a linear mixed model, and we will compare the evolution of the consumption of non-opioid analgesic drugs with a mixed model, following a Poisson distribution. The proportions of patients with pain at H24 and H48, as the rate of local and systemic complications during the follow-up will be compared using logistic regression. The total hospital consumption of morphine equivalent in the first 72 h will be assessed by Poisson regression. Pain intensity at the pericardiac drain removal at H24 will be assessed by linear regression. Time to resuscitation censored at 30 days, time to extubation, time to recover bowel movements, and time to return to preoperative weight will be assessed by survival analysis using a semi-parametric Cox model. The distribution of postoperative complications will be compared by multinomial regression. Satisfaction with the block procedure and the main painful area at H24 will be presented descriptively in the groups.

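### The block-specific tolerance endpoint omits pneumothorax and mediastinitis, two of the five major adverse effects that the protocol itself attributes to the blocks

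*Protocol article*

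**What the plan says.** In the protocol article, Secondary outcomes defines the tolerance comparison as "the proportion of patients with at least one local complication of regional anesthesia" and then lists the qualifying events: "systemic intoxication to local anesthetics within 3 h after injection", and "hematoma or infection at the puncture site during the 30 days after the surgery (D30"). The list is written as complete.

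The Safety section gives a longer list: "The major potential adverse effects linked to SPIP and DPIP are pneumothorax, mediastinitis, hematoma, puncture site infection, and intoxication with ropivacaine". It adds that "A chest X-ray is systematically realized at ICU admission, and this investigation will allow to detect the presence of a pneumothorax".

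Other provisions bear on the point:
- Secondary outcomes also compares the proportion of patients with at least one major in-hospital postoperative complication. The events are listed in Table S.2 of the supplement, which is not at hand.
- Follow-up records complications possibly linked to the block at ICU admission, local or systemic complications at the later visits to 72 h, and puncture-site or postoperative complications at day 30.
- Safety collects serious adverse events to day 30 and provides for discussion of their imputability to the allocation group.
- Statistical analysis states that "the rate of local and systemic complications during the follow-up will be compared using logistic regression", as an exploratory analysis and without restating which events count.

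**The concern.** The tolerance endpoint is the one between-arm comparison built to show harm from the blocks. Its event list should match what the protocol regards as the blocks' major harms, and it does not.

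Pneumothorax is the more awkward omission. The trial looks for it in every patient, yet does not count it in the tolerance comparison. It is also an event on which the two blocks could plausibly differ. The DPIP injection is made deep to the internal intercostal muscle, and for that block "The lowering of the pleura during the injection is a quality sign". The SPIP injection is made superficial to the external intercostal muscle.

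At stake is the benefit/risk evaluation announced in the Discussion. The protocol sets up no independent monitoring committee, so much of the comparative safety evidence will come from the end-of-trial tables. A tolerance result that shows no difference could be read as covering all the named risks when it covers only three of them.

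**Working it through.** **1. The two lists side by side (protocol article)**

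| Major adverse effect named in Safety | In the tolerance endpoint (Secondary outcomes)? |
|---|---|
| Ropivacaine intoxication | Yes, within 3 h |
| Hematoma | Yes, at the puncture site, to D30 |
| Puncture-site infection | Yes, to D30 |
| Pneumothorax | No |
| Mediastinitis | No |

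Covered: 3 of 5. Missing: 2 of 5.

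**2. Figures in the plan.** The plan gives no event rate or power for tolerance. Its only size figure is for the primary endpoint, and it reproduces: n = 2 × (1.96 + 0.842)² × 18² / 8² = 79.5, so 80 per arm. With 5% loss, 240 / 0.95 = 252.6, so 253, or 255 if rounded up arm by arm. The stated 254 lies between. Nothing in this point changes that calculation.

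**3. What the omission could hide (assumed rates).** Suppose the three current components occur in 5% of both block arms, and pneumothorax occurs independently in 1% (SPIP) and 5% (DPIP).
- Current endpoint: 5% versus 5%, difference 0.
- With pneumothorax added: 1 − 0.95 × 0.99 = 5.95% versus 1 − 0.95 × 0.95 = 9.75%, difference 3.8 percentage points.

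**4. What adding the events can achieve.** With n = 80 per arm, two-sided 5% and the normal approximation,

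power = Φ{ (|p₂ − p₁| − 1.96 √[2p̄(1 − p̄)/n]) / √[(p₁(1 − p₁) + p₂(1 − p₂))/n] }, where p̄ = (p₁ + p₂)/2.

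| Assumed pneumothorax risk, SPIP vs DPIP | Power |
|---|---|
| 1% vs 3% | 14% |
| 1% vs 5% | 32% |
| 1% vs 10% | 71% |

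For 1% vs 5%: (0.04 − 1.96 × 0.02697) / 0.02679 = −0.48, and Φ(−0.48) = 0.32.

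If no event is seen in 80 patients, the exact two-sided 95% upper limit is 1 − 0.025^(1/80) = 4.5%.

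A formal test would therefore usually be inconclusive. Events would still be seen if reported: at a true risk of 3%, the chance of at least one in 80 patients is 1 − 0.97⁸⁰ = 91%.

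**The case against.** The strongest reply is that the tolerance endpoint is not the only safety comparison. Table S.2 may well list pneumothorax and mediastinitis, and that complication endpoint is compared between groups. Block-linked complications and serious adverse events are collected throughout. The analysis sentence on local and systemic complications does not confine itself to the three events. A narrow composite is also defensible: surgery itself can cause pneumothorax and mediastinitis, and adding them brings background events.

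Much of this stands. A reader might infer that the whole SPIP versus DPIP safety comparison leaves out the pleural risk. The documents do not support that, because Table S.2 is not shown and the events would be recorded in any case. Nor do they state that DPIP carries more pneumothorax than SPIP: Safety attributes the risk to both blocks without ranking them, and the lowering of the pleura is described as a sign of quality, not of harm.

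A reader might also infer that the logistic model must fail because the standard arm cannot have events. That goes too far:
- Comparing blocks with standard care on tolerance is not clearly specified.
- A rescue nerve block, whose use is recorded at H24, means zero events are expected in the standard arm but not guaranteed.
- Statistical analysis already plans absolute differences with 95% intervals.
- Methods for sparse events are ordinary content for a statistical analysis plan.
- The limit for an arm with no events among about 85 patients (3/85 = 3.5% one-sided, 4.2% exact two-sided) holds whatever the composite contains, so it does not measure the omission.

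The mismatch itself is not answered. The endpoint's list is closed and comes from the article, so it is not a detail left to an unseen document. The label of local complications does not explain the exclusion, since systemic intoxication is counted. If Table S.2 does include the two events, an any-event composite of surgical complications would dilute them. A pneumothorax seen on X-ray but judged neither major nor serious might then enter no clearly defined comparison.

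**Conclusion.** The point holds as an inconsistency between two sections of the protocol article. The endpoint meant to compare tolerance covers 3 of the 5 major adverse effects that the protocol attributes to the blocks, and one of the two missing events is looked for in every patient. Whether any other prespecified comparison captures the two events depends on Table S.2, which cannot be checked here. If it does, they are pooled with general surgical complications.

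The consequence is limited. This is an exploratory safety endpoint, and the primary analysis and sample size are unaffected. The event rates used in the working are assumptions, since the documents give none. Over the range tried, power for pneumothorax alone is 14% to 71%, so correcting the endpoint gives complete reporting by arm and not a powered test. It is still worth correcting, because the stated aim is a benefit/risk judgement and the change costs little.

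**What to change.** Reconcile Secondary outcomes with Safety:
- Prespecify pneumothorax on the ICU-admission X-ray and mediastinitis to D30 as components of the tolerance endpoint.
- Report every component separately by arm, as a count and percentage, with risk differences and exact 95% intervals.
- For pneumothorax and mediastinitis, show all three arms, with the standard arm as the surgical background rate.
- Compare puncture-site and local-anesthetic events between SPIP and DPIP.
- State whether Table S.2 also lists pneumothorax and mediastinitis, so that the reader knows where each is counted.
- Label the comparison as descriptive.

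The cost is mainly wording, because the X-ray and the complication follow-up to D30 are already planned. The drawback is that surgical events add background noise to the composite, which is why the components should be shown separately. No change to sample size or to the testing hierarchy is needed.

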### Follow-up

Day 0 (D0) is the day of surgery with hour 0 (H0) corresponding to the time of randomization. The delay between randomization, achievement of the intervention for the arms with PNB, and admission to the ICU will be negligible (a few minutes). Ten visits are scheduled after the inclusion, and the summarized plan is presented in Fig. 1. The follow-up will begin at the pre-inclusion visit during the anesthesia consultation aiming to collect demographic data, type of surgery, medical history, vitals parameters (cardiac rate and blood pressure), and the pre-operative QoR-15 score.

The inclusion visit will be realized at the end of the surgery during the skin closure. Once the patient is included and allocated to one arm, the block will be carried out according to the allocation group before the transfer to the ICU. The operator’s satisfaction will be assessed on a Likert scale at this time. Perioperative surgical and anesthesia data will be recorded.

On ICU admission, the collected data will be the hemodynamic parameters, the biological values, and a local or systemic complication possibly linked to block. The intensity of pain at rest and during effort, the consumption of analgesics, and the notification of local or systemic complications will be collected during the following visits at 3, 6, 12, 24, 48, and 72 h after the surgery. The QoR-15 questionnaire will be completed at H48 and H72. At H24, patients will detail the body localization of the most intense pain, the use of a rescue peripheral nerve block, and the intensity of pain at the removal of the pericardial drains. Morphine equivalents and non-opioid analgesic drugs consumptions will be collected at 4 and 5 days after the surgery. The patient’s weight and the occurrence of bowel movement will be noted at H72 and 5 days after the surgery.

Thirty days after the surgery, the following data will be collected: a puncture site or a postoperative complication, the length of hospital censored at D30 if the patient is still hospitalized, and length of stay in ICU. Potential readmission to ICU will also be notified. If the patient’s condition does not allow him to be contacted directly or by phone, the person in charge of the follow-up will be contacted (e.g., family member or physician).

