## Discussion

The potential benefits of using chest wall blocks in cardiac surgery was highlighted in recent trials. Concerning the SPIP, Zhang et al. found decreases in length of hospitalization, postoperative pain at mobilization and at rest, and even in postoperative analgesic consumption when comparing SPIP to a placebo [30]. These results were corroborated on the pain measured after extubation [31]. Regarding the DPIP, a study highlighted the impact of the technique to reduce postoperative pain, length of hospitalization, and consumption of analgesics within 48 h [15]. This trend was also found in cardiac surgery in the pediatric population [32, 33].

Our study should provide interesting additional data to confirm whether these chest anterior wall blocks are useful for decreasing postoperative pain and improving recovery and then to compare SPIP and DPIP for these criteria. To evaluate the interest of these blocks, we choose the primary criteria focused on patient’s early recovery. Recent international consensus (i.e., the SteP-COMPAC group) highlighted the importance of this patient-centered endpoint in perioperative medicine [23]. The QoR-15 has already shown its reproducibility, sensibility, and ease to use to reveal the quality of postoperative recovery in a unidimensional approach. QoR-15 is increasingly used as an endpoint in randomized trials in anesthesia [24].

If the hypotheses on the effectiveness of the SPIP and/or DPIP are confirmed for the early QoR, associated benefits could be a better patient experience, a lower incidence of postoperative complications (particularly related to opioids consumption), and even an impact on the lengths of hospital stay.

To summarize, this study will compare two types of chest anterior wall blocks versus a standard care with no regional anesthesia in patients scheduled for cardiac surgery with sternotomy, on their early QoR, but also on their pain status. The findings will also provide data on potential local and general complications that could be attributed to these invasive techniques, helping us to evaluate the benefit/risk ratio of the use of chest wall blocks for cardiac surgery.

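### The between-group tolerance endpoint omits pneumothorax and mediastinitis, two of the five major block risks that the protocol names itself

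*Protocol article*

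**What the plan says.** Under Outcomes, Secondary outcomes, the protocol article defines the tolerance comparison as the proportion of patients with "at least one local complication of regional anesthesia: systemic intoxication to local anesthetics within 3 h after injection", followed by "hematoma or infection at the puncture site during the 30 days after the surgery (D30"). The list follows a colon and has no wording that leaves it open. A second safety endpoint in the same section is "the proportion of patients with at least one major hospital postoperative complication", whose components are in Table S.2 of the supplement (not shown).

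The Safety section states: "The major potential adverse effects linked to SPIP and DPIP are pneumothorax, mediastinitis, hematoma, puncture site infection, and intoxication with ropivacaine". It adds that a chest X-ray is taken systematically at ICU admission and that "this investigation will allow to detect the presence of a pneumothorax". Serious adverse events are collected to 30 days, "whose imputability with one of the allocation groups will be discussed".

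The Follow-up section has staff record "a local or systemic complication possibly linked to block" at ICU admission, with local or systemic complications notified again at the visits up to 72 h and puncture-site or postoperative complications at day 30.

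The Statistical analysis section compares the rates of local and systemic complications by logistic regression, among the analyses labelled exploratory. It also plans a multinomial regression of the distribution of postoperative complications.

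**The concern.** The Safety section and the tolerance endpoint should describe the same set of harms, and they do not. The protocol regards pneumothorax as a block risk and relies on a systematic X-ray to find it, then leaves it out of the one comparison that is meant to show how well the technique is tolerated.

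The omission bears on the comparison between the two blocks. By the Intervention section, the deep block is injected between the internal intercostal and transverse thoracic muscles, with depression of the pleura as the sign of a good injection. The superficial block is injected between the pectoralis major and the external intercostal muscle. That pleural injury might differ between the arms is an inference from this anatomy, not a statement in the protocol, but it is a reasonable one. If it did differ, the tolerance proportion as defined would not move. The Discussion expects the safety findings to contribute to the appraisal of the technique, "helping us to evaluate the benefit/risk ratio of the use of chest wall blocks for cardiac surgery".

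**Working it through.** The main check is a comparison of two lists.

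| Major block risk named under Safety | Component of the tolerance endpoint? |
|---|---|
| Pneumothorax | No |
| Mediastinitis | No |
| Hematoma | Yes, at the puncture site, to day 30 |
| Puncture-site infection | Yes, to day 30 |
| Ropivacaine intoxication | Yes, within 3 h of injection |

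The endpoint covers 3 of 5 and omits 2 of 5.

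**Does the word local explain the omission?** No. The first component is systemic toxicity, so the list is not restricted to events at the injection site.

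**Does lack of data explain it?** No. The block is given before transfer to the ICU and the systematic X-ray is taken on arrival, so it follows the block. Complications are then followed to day 30.

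**Do the other routes put the events into the tolerance comparison?**
- The Follow-up wording is open, but it describes data capture and not an endpoint.
- Serious-event reporting discusses imputability case by case. No between-arm comparison is stated for it, and a pneumothorax seen on X-ray that does not meet seriousness criteria need not enter it.
- The logistic regression of local and systemic complications has no definition in the article other than the list under Secondary outcomes.
- Table S.2 and the multinomial regression may cover either event among general complications. This cannot be checked, and it would not alter the tolerance proportion.

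**Scale.** The plan gives no figure for the tolerance endpoint, so there is none to reproduce. Only the arm size is needed: 254 / 3 = 84.7, about 85 per arm.

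As an illustration, suppose (assumed counts, not a predicted rate) 3 of 85 patients with the deep block and 0 of 85 with the superficial block have pneumothorax as their only block injury. As written, the endpoint scores 0/85 against 0/85. With pneumothorax counted, it scores 3/85 = 3.5% against 0/85. The two-sided Fisher p for that table is 2 × (85 × 84 × 83) / (170 × 169 × 168) = 2 × 592,620 / 4,826,640 = 0.25. The description of harm changes; a test at 0.05 does not become significant.

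For reading any single component: with 0 events in 85, the exact two-sided 95% upper limit is 1 − 0.025^(1/85) = 4.2%. This holds for any zero count at this size. It shows only that an absence of events in an arm would be weak reassurance, whichever component is concerned.

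**The case against.** The strongest case against is that the omission is a defensible choice. Every patient has a sternotomy and an internal jugular catheter, and one randomization stratum has an internal thoracic artery graft. Pneumothorax and mediastinitis will therefore occur for reasons unrelated to the block, and adding them would dilute a block-specific proportion. They may already be compared between arms through Table S.2 and the multinomial regression, and what an article leaves to a supplement is not a fault. This stands in part: it argues against relying on a single enlarged composite, and it rules out any claim that the events are nowhere compared. It does not explain why a list presented as the tolerance of the technique leaves out two risks that the protocol attributes to that technique. Reporting each component by arm meets the dilution argument, because the standard group shows the background rate.

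A reader might infer more than the documents support, in four ways.
- That these two events cannot register as block harm at all. They can: through the complications recorded as possibly linked to the block, and through imputability assessment if serious.
- That naming pneumothorax and mediastinitis first ranks them as the most important risks. The sentence is a list and states no ranking.
- That the benefit/risk statement in the Discussion will rest on the defective proportion. The Discussion refers to local and general complications, which is broader than this endpoint.
- That a conclusion would be reversed. The illustration above gives p of about 0.25, and the endpoint is exploratory.

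**Conclusion.** The point holds in a limited form. As written, pneumothorax and mediastinitis cannot count in the between-group tolerance endpoint, although they are two of the five major block risks listed under Safety. They are not unrecorded or unattributable, and whether they are compared between arms as general complications depends on Table S.2, which is not shown.

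The effect is confined to one exploratory secondary endpoint. The sample size, power and type I error plan are untouched. The conclusion rests on reading the list under Secondary outcomes as closed, which its wording supports, and on that list also defining the complication rate analysed by logistic regression, since no other definition is given. It is a worthwhile, low-cost correction and not a threat to the trial's main result.

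**What to change.** Align the Secondary outcomes, Safety and Statistical analysis sections:
- Add pneumothorax (on the ICU-admission chest X-ray or later) and mediastinitis (to day 30) as tolerance components.
- Report each component separately by arm, in all three groups, counting events whatever their attributed cause, so that randomization and not case-by-case judgement separates block from surgical causes.
- Keep the existing three-component proportion visible beside the extended one.
- State in the Statistical analysis section that the logistic regression of local and systemic complications uses these definitions, and keep it exploratory.

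The cost is outcome wording and one table, because the systematic X-ray and the day-30 follow-up are already planned. The drawback is the background rate from surgery and central venous access in every arm. It dilutes the combined proportion, so the interpretation should rest on the component-level results with their confidence intervals.
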